## Abstract

**Background:**

The process of digitization should simplify our work and improve related processes (i.e. quality, transparency). Moreover, it enables the home office, which is greatly expanded due to the current pandemic. Regarding workplace health, it should be noted that with increasing digitization, physical activity decreases, and as a result, the number of work-related diseases will increase. On the other hand, increasing digitization also offers promising opportunities for new approaches to workplace health promotion. With these positive as well as negative effects in mind, we designed a workshop to increase physical activity at work. This protocol describes our approach to a live workshop concept.

**Methods:**

We use a randomized controlled trial with two intervention groups: a live workshop with and without additional reminders. The workshop intervention design consists of a baseline measurement, two workshops, and one follow-up measurement. Each workshop takes place in small groups (*n* < 11). We use a randomized allocation to both groups. To control for health-related effects and the expected behavior change we examine (i) physical activity (i.e. active time, taken steps, etc.) by a tracking device (ii) physical wellbeing, motivation, and volition by an online questionnaire, and (iii) participants also report physical activity by a diary. All measurements are taken one week before the respective workshop and 24 weeks after the initial baseline measures.

**Discussion:**

A live workshop offers advantages such as very personal interactions and a low technical effort. However, during the current pandemic, there are some limitations (i.e. small groups, pay attention to hygienic guidelines). Based on the upcoming experiences of this workshop, a web-based approach might offer some advantages (i.e. easier daily implementation, independent from a participant’s location) regarding home office workplaces and the increasing digitization. On the other hand, there are also mandatory requirements as a stable internet connection and technical equipment (i.e. webcam, microphone). Overall, a step by step development of a web-based workshop, based on the experience of the live workshop, can be regarded as advantageous.

**Trial registration:**

Since this article reports a health promotion intervention concept with human participants, we registered it in the German Clinical Trials Register (DRKS). Number:DRKS00021512, Date:30.10.2020.

## Introduction

Today, digitized office workplaces are equipped with a computer, printer, telephone, webcam, and in the best case height-adjustable desks to meet ergonomic requirements. The latter also enables office workers to switch their position between sitting and standing, to trigger some physical activity. However, most office and home-office workplaces still have no height-adjustable desk and office workers spend most of their working hours sitting (i.e. while working on the computer, attending meetings or conferences, or making telephone calls) [1]. Additionally, during the after-work hours, people relaxing on the couch, in front of the TV, and use the benefits of a smart home, which in turn increases the sedentary behavior [1]. Regarding the described behavior, it is obvious that the process of digitization might be also accompanied by negative effects (i.e. reduced physical activity and mental stress) [1, 2]. Especially, since the current pandemic is causing a rapid development of digitization, it can be feared that inactive behavior increases.

Importantly, inactivity increases the risk of lifestyle diseases like cardiovascular events, type II diabetes, or cancer [3]. For example, increased daily sitting times (i.e. six to eight hours in total) are associated with a higher risk of mortality [4, 5]. Additionally, it is accepted that long periods of sitting or inactivity are associated with musculoskeletal disorders (MSD, i.e. back pain). MSD was the most frequent reason for days of incapacity to work in 2014 [6] and in the current absence from work report [7], MSD are still the second most frequent reason.

One interesting approach to countermeasure inactivity is a twofold strategy of reducing sitting time and increasing physical activity [8]. The first one is strongly influenced by habits [9], thus interventions should consider approaches for behavioral change. The second part of the strategy is as well important, as the negative effects of long periods of sitting can be positively influenced by increased physical activity [3, 10]. Moreover, a reduced sitting time without physical activity shows only minor effects [11].

A recent review indicated that exercise programs, workplace support, participative approaches, or cognitive-behavioral programs are beneficial [12]. In this vein, multi-component programs, which include the individual, the organization, and the workplace, should be preferred [12–15]. For example, [15] reported three multi-component interventions in which height-adjustable desks combined with behavioral interventions (e.g. goal-setting, self-monitoring, problem-solving, etc.) were used. In this review, the authors showed that multi-component interventions and single workplace-related interventions (e.g. height-adjustable desks) are most effective in reducing sitting time. For multi-component approaches, the literature showed moderate but heterogeneous evidence regarding the reduction of sitting times at the workplace [16, 17]. Despite these positive results, more research is needed, as the number of multi-component studies compared to single intervention studies is still too small [13, 15, 17].

Another review that focused on a reduction of sitting time described approaches and techniques, based on the Behavior Change Wheel [18], and named four principal intervention approaches: (i) knowledge transfer, (ii) efforts at persuasion, (iii) environmental restructuring, and (iv) training [19]. The authors also described other behavioral change techniques (i.e. problem-solving, goal-setting, self-monitoring, social support, feedback), which have also been promising. Furthermore, other researchers reported that self-efficacy and action planning can influence the implementation of physical activity positively [20]. Self-efficacy is defined as a person’s beliefs that events in their own life can be influenced through their abilities [21, 22]. Regarding the occupational context, self-efficacy can be subdivided into (i) occupational, (ii) social, (iii) self-oriented emotional, and (iv) other-oriented emotional [23]. Additionally, the authors refer to some studies that describe positive associations between self-efficacy and healthy work. Action planning is one of the different techniques towards a behavioral change [19] and includes the “when”, “where” and “how” of planned behavior [20]. These theoretical constructs are quite useful, since a self-efficacy questionnaire, for example, can also provide information about the effectiveness of action plans [24]. However, the constructs are also discussed critically. Studies have shown that only action planning has direct effects on physical activity whereas self-efficacy or other social-cognitive factors have indirect [24, 25] or no effects [26, 27]. Our approach refers to both the above-mentioned principles for a behavioral change as well as a social-cognitive process model (i.e. Health Action Process Approach, HAPA [28, 29]) that includes self-efficacy and action planning. The latter is described more detailed in the methods section.

A further aspect of promising workplace interventions is the usage of reminders (i.e. advertising or describing additional content, offering assistance, or reminding workshop content) to stabilize the favored behavior. Previous studies showed that text messages (e.g. per short message service, SMS) have short term effects regarding strategies of disease prevention and management (e.g. healthier diet, increased physical activity) [30] or achieving behavior change goals (e.g. eating more vegetables, increased walking time per day) [31]. In contrast, a review of cue-reminders (i.e. objects that were introduced during the intervention and should remind a target behavior) showed insufficient evidence [32]. Many of those studies differed regarding the frequency of reminders, but some results indicate that: (i) frequent reminders are more effective [33], (ii) there should be a personal contact [33], and (iii) technology-based strategies (e.g. Email, SMS) seem to have small-to-moderate positive effects on engagement compared to no strategy [34]. Thus, reminders seem to be advantageous for behavior change interventions.

As an intervention, we planned a group-based participatory workshop including a knowledge transfer of health behavior at work, an interactive discussion about how to deal with opportunities and barriers of increased physical activity practice sessions, and action planning regarding increased physical activity and reducing sitting times at the workplace. The HAPA postulates that health behavior change requires both a motivational and a volitional phase. After forming the intention to engage in a certain health behavior in the motivational phase, self-regulatory strategies such as planning are essential for behavioral enactment [29]. During the workshop participants are supported in formulating action plans, that help to bridge the *intention-behavior gap* [35] and might facilitate engagement in physical activity and reduction of sitting times at the workplace. Results of a current systematic review indicated that physical activity is in turn associated with increased well-being [36].

The participation should motivate and offer new perspectives of increasing physical activity at the workplace. We have also designed the workshop in such a way that our concept can be used in various companies. In this first step, we want to prove our concept in medium-sized organizations. Due to the current pandemic situation, there is an increasing number of people working in separate offices without any contact with other co-workers. To ensure that these changes do not lead to increased inactivity, new work-related health offers or activity programs should be established. We developed a workshop which takes all the above-mentioned points into account. The use of computer prompts combined with providing information reduces sitting time on average by 14 to 96 min per day*.* In this early stage, we want to prove the concept of our live approach in small groups and hypothesize that the participants show positive health effects (i.e. well-being, decreased MSD) and positive adaptations in their health behavior (i.e. increased physical activity). We hypothesize that additional reminders improve health-related effects. In addition, we want to develop our workshop design in the framework of eHealth applications or a web-based solution, since the integration of such approaches might improve the efficiency of health programs at work [37].

## Methods

### Participants

We recruit office desk workers aged between 18 and 67 years from different organizations (i.e. public administration with standard office workplaces) in Germany. Two intervention lines are planned: one live workshop group with and one without reminders. After attending the first workshop participants in the appropriate intervention group will receive reminders via e-mail twice a week. The e-mails remind the participants of the possibilities to be physical active at the work place previously introduced through the workshop. Overall, eight e-mails will be sent until participants answer the second online survey one month after participating in the workshop. We use a randomized allocation of the participants to both groups. As inclusion criteria, we define an age group between 18 and 67 years and the employee council of each institution has to approve the participation. Additionally, participants are asked not to take part in other studies during the time of the workshop intervention. Participants are excluded if they take part in only one workshop or do not fill in the questionnaires (missing answers > 30%) appropriately. All participants will be informed about the content and objectives of our study, they can ask questions, and they can withdraw from the participation at any time. As a prerequisite for participation, participants of our study sign a declaration of consent. A meta-analysis [38] revealed small intervention effects of workplace physical activity interventions (d = 0.21). Based on this assumption, power-analysis (G-Power 3.1) indicated in sum 168 participants for an ANOVA with repeated measures (within-between interaction). Our calculation included *f* = 0.11, *α* = 0.05, β = .80, three groups, and three measurements.

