### Study-aim and procedure

Our study aims to examine health-related effects from two slightly different live workshops with office workers. Therefore, we contact health counselors at various companies in Germany. If they are interested in participating in our study, further details will be discussed and the employee council and management level will be involved. If the management approves our study, the health counselors will be interviewed and will help to distribute the information among the employees (i.e. via email). In an email, participation in one of our groups will be clearly explained. The study information and the consent form are attached to this email, with additional contact details of the study supervisors (i.e. regarding upcoming questions). As a prerequisite for participation, these documents must be signed and returned. The participants have the opportunity to choose a suitable date from a list of workshop dates in their company. Each participant receives a link to participate in the online questionnaire as well as an activity diary one week before their first workshop. Additionally, we use accelerometers to objectively measure physical activity during this week. Accelerometers with instructions, activity diaries and an online survey will be sent to all consenting participants for data collection. The instructions explain how to attach the accelerometer to the participant’s thigh and hip. Previous studies have indicated three days are sufficient to observe a stable pattern of physical activity [39]. Not wearing the accelerometer for 3 successive days leads to exclusion of the participant from the study.

This procedure is repeated one week before the refresher workshop and after six months. We have no blinding of our workshop supervisors and outcome assessors or data analysts. In each group data collection starts one week before the first workshop. The study procedure is presented in Fig. 1.

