### Statistics

All data are processed to enhance quality; for example, in case of missing data, we conduct a missing value analysis (MVA) with a subsequent imputation procedure. Outliers are checked manually. Then, it is planned to perform analyses for repeated measurements of physical wellbeing, HAPA subscales, and the results from the physical activity diary. Results from the Nordic Musculoskeletal Questionnaire are analyzed descriptively. For all analyses, the significance level is set to 0.05.

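### Excluding participants for missing the refresher or for incomplete later surveys selects on behaviour after the reminders start, so the reminder comparison can be biased

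*Protocol article*

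**What the plan says.** All references are to the protocol article.

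- **Allocation** (Participants): "We use a randomized allocation of the participants to both groups". The two groups are the workshop with and the workshop without reminders. The time of randomisation is not given.
- **Exclusion** (Participants): "Participants are excluded if they take part in only one workshop or do not fill in the questionnaires (missing answers > 30%) appropriately". The rule does not say which workshop or which survey is meant.
- **Start of reminders** (Participants): "After attending the first workshop participants in the appropriate intervention group will receive reminders via e-mail twice a week".
- **End of reminders** (Participants): "Overall, eight e-mails will be sent until participants answer the second online survey one month after participating in the workshop".
- **Baseline** (Study-aim and procedure): "Each participant receives a link to participate in the online questionnaire as well as an activity diary one week before their first workshop".
- **Later measurements** (Study-aim and procedure): "This procedure is repeated one week before the refresher workshop and after six months".
- **Missing data** (Statistics): "in case of missing data, we conduct a missing value analysis (MVA) with a subsequent imputation procedure".
- **Expected action of reminders** (Introduction): "technology-based strategies (e.g. Email, SMS) seem to have small-to-moderate positive effects on engagement compared to no strategy".

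The Introduction also makes a benefit of reminders one of the trial's hypotheses, so the randomised contrast is a question the trial means to answer.

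**The concern.** The e-mails are the only randomised difference between the two workshop arms. An exclusion that depends on what people do after the e-mails begin can remove different kinds of people from each arm, and the arms that remain are no longer those that randomisation made comparable.

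The bias could run either way. If reminders hold on to less motivated people who would otherwise have dropped out, the reminder arm keeps weaker responders and looks worse. If frequent e-mails put some of these people off, the reminder arm loses them and looks better. Motivation and volition are themselves measured outcomes, so a link between staying in the study and the outcome is plausible.

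The rule is written into the protocol. It is not a detail that the text leaves to an analysis plan.

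**Working it through.** **Step 1: which exclusions can reminders influence?**

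| Trigger | When it is settled | Can reminders affect it? |
|---|---|---|
| Baseline survey more than 30% missing | One week before workshop 1 | No |
| Workshop 1 missed | Before the first e-mail | No |
| Survey 2 more than 30% missing | About one month after workshop 1, at the end of the e-mail period | Yes |
| Refresher missed | One week after the second measurement | Yes |
| Survey 3 more than 30% missing | Six months | Yes |

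Three of the five triggers fall after the arms diverge.

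**Step 2: is anyone excluded brought back?** The Statistics section plans imputation, but imputation fills gaps for people who are in the data set. It does not restore people who have been removed. No section describes an analysis of all randomised participants. The accelerometer non-wear rule under Study-aim and procedure speaks of exclusion from the study itself, which makes it harder to read these rules as defining only a secondary analysis set.

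**Step 3: how large could the effect be?** The document gives no retention rates and no correlation between engagement and outcome, so there is no figure of the plan's own to reproduce here. The inputs below are assumptions.

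Model: standardised follow-up score, no true reminder effect. A person is retained if a latent engagement score exceeds a cut-off, and this score has correlation r with the outcome. With retained share p, cut-off c = z(1 − p) and standard normal density φ, the mean of those retained is r·φ(c)/p. The false difference, reminder minus no reminder, is

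bias = r·[φ(c_R)/p_R − φ(c_N)/p_N].

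- p = 0.85: φ/p = 0.2332/0.85 = 0.274
- p = 0.75: φ/p = 0.3178/0.75 = 0.424
- p = 0.70: φ/p = 0.3477/0.70 = 0.497

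| Retained with / without reminders | Multiplier of r | r = 0.3 | r = 0.5 |
|---|---|---|---|
| 80% / 80% | 0 | 0 | 0 |
| 85% / 75% | −0.149 | −0.045 SD | −0.075 SD |
| 85% / 70% | −0.222 | −0.067 SD | −0.111 SD |

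The negative sign (against reminders) follows from assuming that reminders raise retention and that engagement goes with better scores. Other mechanisms could reverse it. In this model the bias is zero if retention is equal or r = 0.

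**Step 4: the planned test concerns change.** The sample-size paragraph names a within-between interaction, which compares change between groups. If engagement correlates r_post with the follow-up score and r_base with the baseline score, and both have equal SD, the 85%/75% case becomes

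bias in change = −0.149·(r_post − r_base).

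With r_base = 0 this is the level result above. With r_post = 0.5 and r_base = 0.3 it is −0.149 × 0.2 = −0.030 SD. With equal correlations it is zero.

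**The case against.** The strongest reply is that differential retention is not shown. The e-mails are described as recalling ways of being active at work. The text does not say that they prompt refresher attendance or survey completion. Under Study-aim and procedure, the institution's health counsellor promotes every workshop and measurement, with no distinction by arm, which tends to even out attendance. This stands as far as it goes. It means that bias cannot be asserted as a fact, but it does not remove the route by which bias can arise, and the Introduction's remark on engagement makes that route plausible.

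A reader might infer three stronger things that the document does not support.

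- **That every exclusion under the rule follows the reminders.** The baseline survey and the first workshop come before them.
- **That the rule contradicts the missing-data plan.** Imputing up to a 30% threshold and excluding above it are compatible. The difficulty is only that imputation cannot reach people already removed.
- **That the sample size is evidence for the bias.** The stated total of 168 reproduces (power 0.803 for three groups, assuming a correlation of 0.5 between measurements and sphericity). If 20% were excluded, 134 would remain and power would be about 0.69. That is a separate matter of dropout allowance, and it concerns a three-group test, not the two-arm reminder contrast.

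It is also fair to object to setting the illustrated bias against the planning effect of d = 0.21. That figure is for workplace activity interventions in general, not for adding reminders.

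**Conclusion.** The concern holds in a limited form. Where the exclusion is triggered by a missed refresher or by the second or third survey, it conditions on behaviour after the randomised e-mails have begun, and the document provides no as-randomised analysis. The reminder comparison can therefore be biased. Bias requires exclusions that differ between arms, in number or in kind, and that are related to outcome. Neither condition can be checked from the document.

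On the assumed 85% versus 75% retention with r of 0.3 to 0.5, the false difference is about 0.045 to 0.075 SD in the follow-up score. It is less on the change scale if engagement also correlates with baseline, and nil if the two correlations are equal. These figures show what is possible and do not estimate what will happen in this trial.

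**What to change.** Do not use refresher attendance or completeness of post-baseline questionnaires as exclusion criteria for the main comparison. State instead that:

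1. all randomised participants are analysed in their allocated arm, using a mixed model or the imputation already planned;
2. participants who miss the refresher still receive the planned surveys;
3. attendance at both workshops and at most 30% missing answers define sensitivity analyses only.

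Both the mixed model and standard imputation assume data missing at random, so they do not remove bias if dropout depends on unobserved outcomes.

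The cost is modest but goes beyond wording, because non-attenders must be followed up. The effect estimate may be somewhat diluted and more values will be imputed. Data Availability says that the study has not started, so the change can be made before any data are lost. Follow-up not collected from excluded people could not be recovered later.

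### The sample size is tied to d = 0.21 but computed with f = 0.11, apparently 0.105 rounded up; for f = 0.105 the 168 participants give about 76% power, not 80%.

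*Protocol article*

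**What the plan says.** The sample size is justified in three consecutive sentences of the Participants section (Methods) of the protocol article.

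- The planning effect: "A meta-analysis [38] revealed small intervention effects of workplace physical activity interventions (d = 0.21").
- The result, linked explicitly to that effect: "Based on this assumption, power-analysis (G-Power 3.1) indicated in sum 168 participants for an ANOVA with repeated measures (within-between interaction").
- The inputs: "Our calculation included *f* = 0.11, *α* = 0.05, β = .80, three groups, and three measurements".

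The section gives no formula for turning d into f, no correlation between repeated measurements and no sphericity value.

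**The concern.** The text presents 168 as the consequence of d = 0.21, but the effect size in the calculation is slightly larger than d = 0.21 yields under the conversion that seems to have been used. Required sample size varies roughly with 1/f², so rounding f upward before solving for N makes N too small for the effect that is cited. The inputs also give β as .80. Read literally, β is the type II error rate, which would mean 20% power.

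At stake is how a non-significant interaction would be read. A reader would take the trial to have had 80% power for d = 0.21, when under the plan's own model it had somewhat less.

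**Working it through.** **Inputs.** From the Participants section: d = 0.21, f = 0.11, α = 0.05, k = 3 groups, m = 3 measurements, N = 168, and a within-between interaction in a repeated-measures ANOVA. Assumed, because they are not stated: correlation ρ = 0.5 and sphericity (ε = 1).

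**Formula.** Noncentral F with λ = f² · N · m / (1 − ρ), df1 = (k − 1)(m − 1), df2 = (N − k)(m − 1).

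**Step 1: reproduce the plan.** With f = 0.11 and N = 168:
- λ = 0.0121 × 168 × 3 / 0.5 = 12.20, df1 = 4, df2 = 330; power = 80.3%.
- At N = 165 the power is 79.5%, so 168 is the smallest total with equal groups that reaches 80%.

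The plan's figure is reproduced exactly, which supports the two assumed settings. With sphericity, ρ = 0.49 would give 171 and ρ = 0.51 would give 165. It also shows that .80 was used as power, 1-β.

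**Step 2: trace f back to d.** f = d/2 = 0.21/2 = 0.105, which is 0.11 when rounded up to two decimals. In reverse, f = 0.11 gives d = 2 × 0.11 = 0.22.

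**Step 3: repeat without the rounding.** With f = 0.105 and N = 168:
- λ = 0.011025 × 168 × 3 / 0.5 = 11.11, which is (0.105/0.11)² = 0.911 of the value in step 1; power = 76.0%.
- For 80%: N = 180 gives 79.3% and N = 183 gives 80.04%. So 183 are needed, 15 more than 168 (15/168 = 9%).

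**Step 4: could rounding of d itself explain the gap?** Values from 0.205 to 0.215 give f from 0.1025 to 0.1075 and power at 168 from 73.7% to 78.2%. No d that rounds to 0.21 reaches 80%.

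**Step 5: sensitivity to the conversion.** f = d/2 holds for two equal groups. If 0.21 were the range of means across three equal groups, f would depend on where the middle group lies:

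| Reading of d = 0.21 | f | Power at 168 | N for 80% |
|---|---|---|---|
| Two-group conversion, d/2 | 0.105 | 76% | 183 |
| Three groups, two at one extreme: d√8/6 | 0.099 | 70% | 207 |
| Three groups, one midway: d/√6 | 0.086 | 56% | 276 |

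**The case against.** The strongest reply is that nothing was miscalculated. The article prints f = 0.11, and 168 with 80% power follows exactly from it. This stands: a reader might infer that 168 is an arithmetic error or cannot be derived from the stated inputs, and that would be wrong. The mismatch lies only between the printed f and the d on which the calculation is said to rest.

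Second, f = d/2 is an inference. This also stands. The conversion is plausible because it explains 0.11, but a reader should not conclude that 0.105 is the correct f for this design. Step 5 shows that a three-group reading of d gives smaller values, so on that reading 76% would be too favourable.

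Third, four points of power are small beside the uncertainty in the correlation. At f = 0.105 and N = 168, power is 67% at ρ = 0.4, about 80% at ρ = 0.54 and 86% at ρ = 0.6. That is a fair reason to call the shortfall modest. It does not restore the stated figure, because those correlations do not reproduce 168: with f = 0.11, ρ = 0.4 gives 201 and ρ = 0.6 gives 135.

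Fourth, the group structure could matter more. The Study-aim and procedure section gives the control group only a pre- and post-study questionnaire, so three measurements in all three groups is itself open to question. That is a separate matter. The 76% is conditional on the model that the calculation names.

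Finally, a reader might infer that power is lower still because the article excludes some participants after enrolment and shows no dropout allowance. The document does not support adding this. An article may leave such an allowance to the full protocol, and no expected loss is given.

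**Conclusion.** The point holds as a modest misstatement of a design figure. The article attributes 168 participants and 80% power to d = 0.21, but the calculation used f = 0.11, which is d = 0.22 under the apparent conversion. At f = 0.105 the power is about 4 points lower than stated. This rests on the inferred conversion f = d/2 and on ρ = 0.5 with sphericity, both unstated but supported by the exact reproduction of 168. The β label is a plain slip, because 168 is obtained only when .80 is read as power.

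**What to change.** Restate the figure in the Participants section in one of two ways:

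- 168 analysed participants give 80% power for f = 0.11 (d = 0.22 under f = d/2); or
- 168 analysed participants give about 76% power for d = 0.21 (f = 0.105), with 183 needed for 80%.

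In either case, state the conversion, the correlation (0.5, if that was the setting used) and the sphericity assumption, and write 1-β = .80 where .80 power is meant. Say which contrast d = 0.21 describes. If it is the range across three groups, derive f and the power from that reading.

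The cost is wording only. No additional participants are required. The second option, or a three-group reading of d, makes the stated power less favourable. The article's data availability statement says that the study has not yet started, so the correction can be made before any data exist.

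### The only test the article names treats baseline as an outcome level; for the randomised reminder comparison, adjusting for baseline would be more efficient, by an amount that depends on the effect profile

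*Protocol article*

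**What the plan says.** Protocol article, Participants: the sample size comes from "power-analysis (G-Power 3.1) indicated in sum 168 participants for an ANOVA with repeated measures (within-between interaction"), with f = 0.11, α = 0.05 and "β = .80, three groups, and three measurements". The value .80 is evidently the power. The effect is taken from a meta-analysis that "revealed small intervention effects of workplace physical activity interventions (d = 0.21").

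The timing is in the abstract ("All measurements are taken one week before the respective workshop and 24 weeks after the initial baseline measures") and under Study-aim and procedure ("This procedure is repeated one week before the refresher workshop and after six months"). The three measurements are therefore one before the first workshop, one before the refresher and one at six months. Reminder e-mails start only after the first workshop, so the first measurement is a true pre-reminder baseline.

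On allocation, Participants says "We use a randomized allocation of the participants to both groups", meaning the workshop with and the workshop without reminders. A control group that completes pre- and post-study questionnaires appears under Study-aim and procedure, but it is not described as randomised. The Introduction hypothesises that reminders improve the health-related effects.

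The Statistics section says "it is planned to perform analyses for repeated measurements of physical wellbeing, HAPA subscales, and the results from the physical activity diary" and "For all analyses, the significance level is set to 0.05". It gives no model, no test term and no role for baseline.

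**The concern.** In a within-between interaction over three measurements, baseline is one of the responses. The arms are compared on unadjusted differences between occasions, so all of the baseline noise enters the comparison. Between two randomised arms, any baseline difference is due to chance. A covariate-adjusted comparison subtracts only the part of baseline that predicts the follow-up value, and so has a smaller variance.

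The reminder comparison is the article's randomised contrast and one of its hypotheses. Its confidence intervals would be wider, and its power lower, than the same data allow.

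**Working it through.** **Inputs.** From the article: f = 0.11, α = 0.05, three groups, three measurements, N = 168, d = 0.21. Not in the article, so assumed: the correlation rho between measurements (0.5, range 0.3 to 0.7), compound symmetry, arm size (56 = 168/3, with 84 = 168/2 as the alternative), d = 0.21 as the size of the reminder effect, and how that effect is spread over the two follow-ups.

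**Step 1: the plan's own figure.** Noncentral F with λ = N·f²·m/(1−rho) = 168 × 0.0121 × 3/0.5 = 12.20, on 4 and (168−3) × 2 = 330 df. Power is 80.3%. N = 168 therefore reproduces at rho = 0.5; rho = 0.4 would need 201 and rho = 0.6 would need 135. This confirms that the sizing test is the interaction over all three occasions, baseline included.

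**Step 2: variance at one follow-up** (unit SD, per-participant factor). Change from baseline: 2(1−rho). Baseline-adjusted: 1−rho². At rho = 0.5 these are 1.00 and 0.75, a 25% reduction. The reduction is 35% at rho = 0.3 and 15% at rho = 0.7.

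**Step 3: like-for-like power, two arms of n = 56, both tests on 2 numerator df.**

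- Interaction test: λ = (n/2)·Σ(δ−mean δ)²/(1−rho), where δ holds the arm differences at the three occasions; df 2 and 2 × (112−2) = 220.
- Joint baseline-adjusted test: λ = (n/2)·d′S⁻¹d, where d holds the two follow-up differences and S has diagonal 1−rho² and off-diagonal rho−rho²; df 2 and 2 × (112−3) = 218.

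At rho = 0.5:

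- Equal effect (0, 0.21, 0.21): interaction λ = 28 × 0.0294/0.5 = 1.65, power 19.0%. Adjusted λ = 28 × 0.0882 = 2.47, power 26.7%. With the smaller denominator df of a fully multivariate test (108) it is 26.4%.
- Effect halved at one follow-up: λ = 28 × 0.02205/0.5 = 1.23, power 15.2%. Adjusted λ = 28 × 0.0441 × 1.375 = 1.70, power 19.5%.
- Effect at one follow-up only: λ = 1.65, power 19.0%. Adjusted λ = 28 × 0.0441 × 1.5 = 1.85, power 20.9%.

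Across the range, interaction → joint adjusted test, 56 per arm:

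| Effect profile | rho 0.3 | rho 0.5 | rho 0.7 |
|---|---|---|---|
| Equal at both | 14.7 → 24.2% | 19.0 → 26.7% | 29.3 → 35.8% |
| Halved at one | 12.1 → 17.3% | 15.2 → 19.5% | 22.8 → 26.5% |
| One only | 14.7 → 17.0% | 19.0 → 20.9% | 29.3 → 31.0% |

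With 84 per arm, rho = 0.5 and an equal effect: 26.8 → 38.5%.

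**Step 4: averaging the two follow-ups.** The adjusted mean has variance (1+rho)/2 − rho² = 0.50 at rho = 0.5. With an equal effect, λ = 28 × 0.0441/0.50 = 2.47 on 1 df, power 34.4%. Part of that gain comes from spending 1 df instead of 2: the unadjusted mean change, also on 1 df, already gives 24.6%. If the effect is at one follow-up only, the mean difference is 0.105, λ = 28 × 0.011025/0.50 = 0.62 and power is 12.2%, below the interaction test's 19.0%.

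**The case against.** **The model is named only in a power calculation.** The Statistics section does not exclude a baseline covariate, and covariates are commonly left to an analysis plan. This stands in part: a reader might infer that the article rules adjustment out, and it does not. But the interaction is the one test the article names, it includes baseline as a level, and the Statistics wording does not replace it. The point is about that stated choice, not about missing detail.

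**The interaction test is valid.** This stands. A reader might infer bias from chance baseline imbalance. Under randomisation the imbalance adds variance and no bias, so the issue is efficiency only.

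**The gain is not a fixed amount.** This stands. A reader who looks only at the equal-effect row might infer a guaranteed gain of six points or more. Reminders stop at the second survey, one month after the workshop, and the Introduction itself describes text-message effects as short term. A fading effect is therefore plausible, and the gain is then about 2 to 4 points at rho = 0.5. In every profile checked with matched degrees of freedom it stayed positive.

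**The two-arm figures are not the plan's.** This also stands. The article sizes a three-group omnibus test and gives no effect size for reminders. The percentages illustrate the size of the gain; they do not re-estimate the trial's stated power.

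**Conclusion.** The point holds as a matter of efficiency. For the randomised reminder comparison, the interaction test named in the article leaves unused precision that the planned baseline measurement could supply at almost no cost. The variance formula gives a 25% reduction at one follow-up at rho = 0.5. Like-for-like power gains at d = 0.21 and 56 per arm are about 7 to 8 points for a sustained effect, about 4 if it halves at one follow-up and about 2 if it is confined to one. Correlation, arm size, effect size for this contrast and effect profile are all assumptions.

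Adjustment does not rescue the comparison: under these assumptions the joint test reaches at most about 27% at rho = 0.5 with 56 per arm, and about 39% with 84.

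**What to change.** In the Participants (sample size) and Statistics sections, name the analysis of the reminder hypothesis in the two randomised workshop arms. For each continuous outcome, model the two post-baseline measurements with arm, time, arm-by-time, the participant's own baseline and baseline-by-time as fixed effects, and a random participant effect. Judge reminders by the joint 2-df baseline-adjusted test of the arm difference at the two follow-ups, and report the adjusted difference with its confidence interval at each.

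If the average over both follow-ups is pre-specified as the test instead, state that it loses power when the effect fades. Do not rely on baseline adjustment to make the control group comparable, since it is not described as randomised.

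The cost is wording: no new data are needed, and the Data Availability statement says the study has not started. The model spends a few extra parameters per outcome. The reported quantity becomes an adjusted arm difference instead of an interaction F test. Missing baseline values would fall under the imputation already planned.
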